### Observational study

A concurrent prospective observational cohort study aimed at the individual GP level is planned alongside the trial to evaluate the need for continued neurological education. In this observational study, the effectiveness of neurologic continued education courses offered at regular intervals to GPs by neurologists will be assessed. During the NeTKoH study, these optional sessions are offered once every quarter of the year for continued education credits to the participating NeTKoH-GPs. The analysis of the cohort study will include GPs who participate in at least one neurological training during the entire NeTKoH study.

The primary outcome of this observational study will be the change in self-reported needs in neurological continued education between baseline (i.e., at the study initiation) and end of the study period (after recruitment of the last patient into the trial).

### Process and implementation evaluation

Using the Reach—Efficacy/Effectiveness—Adoption—Implementation—Maintenance (RE-AIM) framework [25], the implementation of NeTKoH will be evaluated to ensure that both interventions (teleconsulting, neurologic continued education) are delivered and implemented as planned and to provide insights on their generalizability. For instance, for the RE-AIM dimension “Implementation,” key elements of the tele-neurologic intervention, such as the number of requested and established teleconsultations, their duration, but also adverse events, e.g., technical problems will be measured. Moreover, the satisfaction of patients and GPs with teleconsultation, as well as the planned adoption of the tele-neurologist’s recommendation, will be analyzed using descriptive statistics. The program costs pertaining to the German healthcare context will also be calculated.

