### Outcomes

Outcomes pertain to the health care system (macro level), the institution (meso level) as well as the individual (micro level).

The primary outcome is the proportion of neurologic problems being solved in the GPs’ practices, measured by the number of patients without an outpatient referral (neurologic/other specialists), inpatient referrals (hospital), or other.

The secondary outcomes include on the macro level: (1) number of hospital stays, (2) length of hospital stay, on the meso level (3) number and types of referrals, and on the micro level (4) time until neurologic appointments, (5) time until specialty diagnostics, (6) quality of life, and (7) health status.

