### Data collection, management, and quality control

Paper surveys for patients and GPs are used to increase the cooperation of GPs and patients during the trial, according to local experts in the study group. However, all paper surveys were created using the software program evasys [21], so that an automatic export of the survey answers at the study center of the participating university hospital (UMG) will be possible for the subsequent evaluation at Charité – Universitätsmedizin Berlin (Charité). The patient and GP paper surveys will be picked up once a month from the GP offices by UMG study personnel.

The standardized telephone interview at 3-month follow-up for patients will be based on a survey, pre-programmed in an evasys web surface, which will be filled out by the interviewer during the call. Since we are expecting attrition to occur, especially at the 3-months follow-up, reasons for dropouts and loss-to-follow-up will be collected.

The NeTKoH-database was programmed using automatic plausibility checks and mandatory fields for data entry. Technical training of the GP offices regarding the use of the teleconsulting system will take place prior to the start of the intervention. On-site monitoring, a feedback loop, and measures to inquire regarding implausible or missing data by the study personnel will be instituted. The study personnel will receive training for the documentation in the NeTKoH database and the evasys web surface. All surveys were piloted before the start of the intervention.

All data collection, handling, transferring, processing and storage will follow the project’s comprehensive data protection concept approved by the responsible data protection officers. The primary and secondary data of NeTKoH will be securely transferred from the data integration center at UMG to the independent evaluation team at Charité for the final analysis and provision of findings to the funding agency. Trained researchers of the evaluation team will code, enter and store the data on the secure Charité server. Only the evaluation team will have access to the final data set.

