There are several limitations to our study. This multi-center stepped-wedge design involving GP practices in the German public health care system can be vulnerable to secular trends, e.g., the COVID-19 pandemic and its impact on care. As with any trial in a real-world setting, we also expect a certain amount of missing information. However, these issues will be addressed with our analysis plan to account for such changes. Given the fact that the trial has to be integrated into the everyday care of the participating GP practices, only a finite number of parameters can be sampled to ensure uninterrupted workflow. However, our interdisciplinary approach during the evaluation planning phase, according to the Framework for Program Evaluation [30], involved clinicians (neurologists and GPs), biostatisticians, epidemiologists, health economists, and implementation specialists, which assured the necessary breadth of information to be collected. Due to local data protection regulations, no data on approached non-participant patients will be collected, thus limiting information on the representativeness of the reached population. This will be accounted for by providing detailed characteristics of the intervention participants.

The strength of NeTKoH is its pragmatic design, allowing for real-world evidence for a teleconsulting intervention in primary care accompanied by continued education for the participating GPs. Of note is that there will be no risk to the recruited patients and the trial will be monitored, and adverse issues will be reported.

Incorporating an evaluation of the implementation based on one of the most used approaches [31] will provide considerable information for policymakers to guide future use and possible scale-up of NeTKoH. Conducting a cost-effectiveness analysis will further provide key information for stakeholders.

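### The only named adverse-event measure is tied to the teleconsultation and has no control-phase counterpart, and the no-risk statement is unsupported; harm can be compared between phases only through indirect outcomes

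*Protocol article*

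**What the plan says.** All references are to the protocol article.

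- **Process and implementation evaluation.** Under the RE-AIM dimension of implementation, the list of what is to be measured opens with the delivery features of the teleconsultation, such as how many take place and how long they last. The same list then closes with the safety item: "but also adverse events, e.g., technical problems will be measured". Adverse events are named nowhere else.
- **Intervention.** Practices in the control phase have no telemedicine device, and their patients have no access to a tele-neurologist.
- **Discussion.** "Of note is that there will be no risk to the recruited patients and the trial will be monitored, and adverse issues will be reported".
- **Outcomes.** The primary outcome is the proportion of problems solved in the practice, "measured by the number of patients without an outpatient referral (neurologic/other specialists), inpatient referrals (hospital), or other". Secondary outcomes include "1) number of hospital stays, (2) length of hospital stay", time until specialty diagnostics, "6) quality of life, and (7) health status".
- **Participant timeline and Table 1.** The primary outcome is recorded directly after the GP appointment (control) or after the teleconsultation (intervention). Hospital stays and time to diagnostics come from a telephone interview of both groups at 3 months. Hospital days come from claims data of two insurers. Table 1 marks each of these as an intervention–control comparison.
- **Data collection, management, and quality control.** Attrition is expected, and "reasons for dropouts and loss-to-follow-up will be collected".
- **Statistical analysis.** Mixed models are planned for all secondary outcomes except referrals.

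**The concern.** The intervention is meant to raise the share of patients who are not referred onward. The foreseeable harm of not referring is a missed or late diagnosis. On the day of assessment such a patient counts as solved, because the primary outcome does not ask whether non-referral was appropriate and is read before harm could appear.

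The one measure called adverse events cannot fill that gap. It sits among the delivery features of the teleconsultation, and its only example is equipment failure. A count of that kind has an intervention column and no control column. The Discussion then states that patients face no risk, and nothing in the article supports this.

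At stake is how the result will be read. The article says the findings are to inform decisions on uptake into standard care. A higher solved proportion could be reported together with a short list of technical incidents and the no-risk sentence. Readers could take that as a safety result, although no clinical adverse outcome had been described as collected alike in both phases.

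**Working it through.** **1. What could show harm in both phases, as described**

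| Measure | Both phases? | Limit as a harm measure |
|---|---|---|
| Adverse events (technical problems) | No, tied to the teleconsultation | Concerns delivery, not patients |
| Number of hospital stays | Yes, 3-month interview | Not separated by urgency or tied to the index problem; needs a patient who can be interviewed |
| Hospital days | Yes, claims data | Two insurers' patients only, about 25% of consultations (sample size section) |
| Time to specialty diagnostics | Yes, 3-month interview | Concerns indicated diagnostics; a diagnosis never pursued gives no time |
| EQ-5D-5L and VAS | Yes, per Table 1 | Participant timeline calls only the first time point feasible, Table 1 lists two; to be reconciled |

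A comparison is therefore possible but indirect. An additional hospital stay may be an earlier, appropriate admission or the result of delay, and the count does not tell them apart.

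**2. Reproducing the plan's own figures**

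*Patient-reported outcomes* (531 control, 310 intervention, d = 0.20, two-sided 0.05, stated power 0.80):
- d / √(1/531 + 1/310) = 2.798
- Φ(2.798 − 1.960) = 0.799. Reproduced, with clustering and time ignored.

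*Primary outcome.* Inputs: I = 33 practices, T = 11 steps, switches of 4, seven times 3, 4 and 4, and n = 3 patients per practice and step. This gives 185 control and 178 intervention practice-steps, hence 555 and 534 patients, as stated.

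The Hussey & Hughes variance, with s = σ²/n, is

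I·s(s + Tτ²) / [(IU − W)s + (U² + ITU − TW − IV)τ²]

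Here U = 178 is the number of intervention practice-steps, W = 3,990 the sum of squared step totals and V = 1,260 the sum of squared practice totals. So IU − W = 1,884 and the second bracket is 10,828. I assume σ² = 0.25 × 0.75 = 0.1875 and τ = CV × 0.20.
- CV 0.25: SE 0.0358, power 0.798 (stated 80%)
- CV 0.20: SE 0.0350, power 0.816 (stated 81%)
- No clustering: SE = √(33 × 0.0625 / 1,884) = 0.0331

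The design is rebuilt closely enough to use for precision.

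**3. Precision of a both-phase adverse-outcome comparison**

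With the plan's 30% loss, n = 2.1 per cell and 363 × 2.1 ≈ 762 patients. The event rates below are assumptions; the article gives none. Without clustering, SE = 0.0331 × √(p(1−p)/0.1875) × √(3/2.1).

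| Assumed rate | p(1−p) | SE | 95% half-width | Half-width with τ = 0.25 × rate |
|---|---|---|---|---|
| 2% | 0.0196 | 0.0128 | 2.5 points | 2.5 points |
| 5% | 0.0475 | 0.0199 | 3.9 points | 4.0 points |

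These rates mean about 15 events (0.02 × 762) and 38 events (0.05 × 762). With so few events, a mixed model with step terms may be unstable, so raw counts should be shown too.

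**4. Sensitivity of the existing hospital-stay comparison**

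Treat it as any stay within 3 months, with 388 control and 374 intervention patients (30% loss from 555 and 534), and ignore clustering and time. For assumed control risks of 5%, 10%, 15% and 20%, the increase detectable with 80% power is about 5.4, 7.0, 8.0 and 8.7 points. Check at 5%: √(0.05 × 0.95/388 + 0.104 × 0.896/374) = 0.0193, and 0.054/0.0193 = 2.80 = 1.96 + 0.84. The planned outcome can show a large excess of stays, not a small one.

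**The case against.** A reader might infer that harm from not referring cannot be compared between phases at all, or that a difference of any size would be invisible. The documents do not support this. Five outcomes that bear on harm are planned between-group comparisons to 3 months, with a mixed model for each. Time to specialty diagnostics bears directly on diagnostic delay. An excess of events leading to admission would enter the hospital-stay count, whatever heading that outcome carries.

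Nor does the article say that nothing is counted in the control phase. The implementation passage is introduced as an example, and technical problems are one instance within it. The Discussion sentence that declares no risk also promises monitoring and reporting of adverse issues, without limiting this to one phase. A condensed article commonly leaves safety definitions and forms to the full protocol or analysis plan. How deaths are recorded is not stated, so it cannot be claimed that they would be missed.

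There is also clinical context. Patients the GP regards as neurological emergencies needing prompt inpatient attention are excluded, and in the intervention phase non-referral follows a neurologist's assessment by video. Both make harm less likely, though neither makes it nil.

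All of this stands, and it limits the point to what the article does state: the only specified adverse-event measure is one-sided, and the no-risk sentence is absolute. The promise to report adverse issues does not repair this, because it comes without a definition, source or comparison.

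**Conclusion.** The point holds in a limited form. As described, the named adverse-event measure exists only where there is a teleconsultation, and the claim of no patient risk has no support in a trial that scores non-referral as success. Between-phase evidence on harm exists, but only through utilisation, timing and quality-of-life outcomes that are not specific to the index problem and are partly incomplete.

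The size of any harm cannot be estimated from the article. What can be estimated is the precision of a proper comparison: about ±2.5 points at a 2% event rate and ±3.9 to 4.0 points at 5%. This assumes 762 followed patients, equal recruitment per practice and step, a normal approximation, and no clustering or a practice-level CV of 0.25. At 2%, a null result would still be compatible with a rate more than twice as high in the intervention phase (2 + 2.5 = 4.5%). The comparison is worth making, but it could exclude only larger excesses and would not justify a statement that risk is absent.

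**What to change.** 1. In the process and implementation evaluation, keep technical problems as an implementation measure and stop presenting them as the example of adverse events.
2. Define adverse patient outcomes identically for both phases, from the initial GP appointment to the 3-month contact: deaths, from the recorded reasons for loss to follow-up and, where available, claims data; hospital stays, already collected; and, if one interview question is added, unplanned admission or emergency visit for the index problem.
3. Report them by phase next to the primary result, as raw counts and with the primary model's step and practice terms.
4. In the Discussion, replace the no-risk statement with one saying that harm will be assessed by this comparison and is estimated with limited precision.

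**Cost.** Wording in the protocol and analysis plan, one table and at most one interview question. Patients interviewed before the change contribute only hospital stays and recorded deaths. In a stepped-wedge trial these earlier patients are disproportionately in the control phase, and no control practices remain in step 11. The added question would therefore be less precise than the half-widths above, which apply to outcomes available from the first step. If interviewing has already ended, the rest of the change can still be made.

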### Health economic evaluation

The economic evaluation will be carried out alongside the trial. It will consist of a cost-utility analysis and three cost-effectiveness analyses. The outcome considered for the cost-utility analysis will be quality-adjusted life years (QALYs) derived from the EQ-5D-5L using German population weights [26]. Effectiveness measures will include the proportion of neurologic problems being solved at the GP’s office, the number of hospital stays, and the length of stay at the hospital. We will include all relevant additional trial costs of the intervention compared to standard care, as well as patient-specific costs stemming from claims data of the participating health insurances. The economic evaluation will be performed from a statutory health insurance perspective.

## Discussion

The increase in neurologic disorders requires strengthening of management and access to neurologic care, particularly in resource-poor rural areas. Tele-neurology in the form of teleconsultations between outpatient GPs and neurologic experts in underserved areas has been identified as an appropriate measure to counter this development [27].

For such interventions in primary care, a CRT with settings as the unit of randomization and patients nested within those settings is particularly suited as it reduces the risk of contamination [28]. Conducting a stepped-wedge design, as an alternative design to a CRT [29] for a tele-neurologic intervention under real-world conditions in a rural area, also has pragmatic considerations. As all clusters receive the intervention by the end of the trial, enhanced recruitment and motivation are likely. Due to the sequential versus simultaneous roll-out of the intervention, this design also has logistic benefits for implementation in a rural area where participating settings can be distant from one another.

We expect that results from this trial will deliver insightful evidence on the effects of tele-neurologic consultations in primary care not only on the patient and organizational (provider) level but also with respect to the healthcare system.

There are several limitations to our study. This multi-center stepped-wedge design involving GP practices in the German public health care system can be vulnerable to secular trends, e.g., the COVID-19 pandemic and its impact on care. As with any trial in a real-world setting, we also expect a certain amount of missing information. However, these issues will be addressed with our analysis plan to account for such changes. Given the fact that the trial has to be integrated into the everyday care of the participating GP practices, only a finite number of parameters can be sampled to ensure uninterrupted workflow. However, our interdisciplinary approach during the evaluation planning phase, according to the Framework for Program Evaluation [30], involved clinicians (neurologists and GPs), biostatisticians, epidemiologists, health economists, and implementation specialists, which assured the necessary breadth of information to be collected. Due to local data protection regulations, no data on approached non-participant patients will be collected, thus limiting information on the representativeness of the reached population. This will be accounted for by providing detailed characteristics of the intervention participants.

The strength of NeTKoH is its pragmatic design, allowing for real-world evidence for a teleconsulting intervention in primary care accompanied by continued education for the participating GPs. Of note is that there will be no risk to the recruited patients and the trial will be monitored, and adverse issues will be reported.

Incorporating an evaluation of the implementation based on one of the most used approaches [31] will provide considerable information for policymakers to guide future use and possible scale-up of NeTKoH. Conducting a cost-effectiveness analysis will further provide key information for stakeholders.

### Trial status

The trial started on October 10, 2021. The last patient will be recruited on October 27, 2024. Results are expected in July 2025.

## Data Availability

Not applicable.

## Abbreviations

CONSORT: Consolidated Standards of Reporting Trials
CRT: Cluster Randomized Trial
G-BA: Federal Joint Committee
GDPR: EU General Data Protection Regulation
GP: General Practitioner
LOS: Length of Stay
NeTKoH: Neurologic Tele-Consultations in GP Practices
QALY: Quality-Adjusted Life Year
RE-AIM: Reach—Efficacy/Effectiveness—Adoption—Implementation – Maintenance
SAP: Statistical Analysis Plan
TIDieR: Template for intervention description and replication
UMG: University Medicine Greifswald
VAS: Visual Analogue Scale
